#### **V3 (Day 1):**

All assessments at this visit should be completed **prior** to participants receiving IMP.

- Concomitant medication check (confirm no systemic corticosteroids have not been used since V1).
- Vital Signs.
- Blood (55ml in total) and urine collection for clinical chemistry (including lipid profile), haematology, urinalysis.
- Blood collection for biomarkers (inclusive within the 55ml as above).
- 12 Lead ECG (triplicate).
- Adverse event assessment.
- Arterial haemodynamics: arterial stiffness, BP and HR.
- Flow mediated dilatation.
- Spirometry post bronchodilator (FEV1 and FVC).
- SNIP (Sniff Nasal Inspiratory Pressure) measurements.
- 6 minute walk test.
- Randomisation and administration of first dose of IMP, and provision of IMP in participant packs.
- Biomarkers Fibrinogen and hsCRP (inclusive within the 55ml as above).
- Blood collection for serum store (inclusive within the 55ml as above).

#### **V4, V5, V6, V7 (Days 14/28/56/84 (All ± 96h)):**

- Concomitant medication check.
- Vital Signs.
- Blood (55ml in total) and urine collection for clinical chemistry, haematology, urinalysis.
- Biomarkers Fibrinogen and hsCRP (inclusive within the 55ml as above).
- Adverse event assessment.
- Dosing of IMP (and provision of new trial medication pack on V5 Day 28, V6 Day 56 and V7 Day 84).
- IMP tablet count.

### **V8 Imaging visit (Days 105-111):**

- The repeat FDG-PET/CT scan can take place any day between Days 105-111.
- The repeat MRI scan (for those participants this applies to) can take place any day between Days 105-111.
- Adverse event assessment.

A clinical report will be generated for the post dose scans as part of Clinical Governance.

### **V9 (Days 109-112):**

During any of these days (but ideally should take place on Day 112):

- Concomitant medication check.
- Vital Signs.
- Blood (55ml in total) and urine collection for clinical chemistry (including lipid profile), haematology, urinalysis.
- Biomarkers Fibrinogen and hsCRP (inclusive within the 55ml as above).
- Blood collection for serum store (inclusive within the 55ml as above).
- Adverse event assessment.
- Arterial haemodynamics: arterial stiffness, BP and HR.
- Flow mediated dilatation.
- SNIP (Sniff Nasal Inspiratory Pressure) measurements.
- 6 minute walk test.
- 12 Lead ECG (triplicate).
- Spirometry post bronchodilator.
- IMP Compliance check and final medication retrieval.

### **12.1.6 V10 Follow-up (Days 120 -126)**

Participants will return to the unit within approximately 1-2 weeks after the last scan, and will undergo the following procedures:

- Physical examination including seated blood pressure (BP) and heart rate (HR).
- Blood (approximately 55mL) and urine will be collected for clinical chemistry, haematology, urinalysis.
- Bloods for biomarkers.
- Adverse event and concomitant medication check.

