|                                                       | 
signs (blood pressure and heart rate) measurements, clinical laboratory tests (including LFT), clinical monitoring /observation and spontaneous and elicited adverse event reporting. Methodology for safety assessments will be on file at the clinical research unit.
 
The Trial Steering Committee (TSC) will provide overall supervision for the trial, to ensure that it is conducted in accordance with the protocol and GCP and to provide advice through its independent chairman.
 |
| Criteria for withdrawal of patients on safety grounds | 
Participants will be withdrawn from the trial if they experience a SUSAR. At the discretion of the PI/CI, participants will be withdrawn if they experience a SAE, which would affect their ability to participate in the trial.
                                                                                                                                                                                                                                                                 |

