## 10.5 Participant Withdrawal Criteria and Stopping Criteria

Reasons for participant withdrawal will be recorded in the electronic Case Report Form (eCRF). Primary reasons for withdrawal may include: SUSAR, adverse event, withdrawal of consent, lost to follow-up, protocol deviation, participant non compliance, lack of efficacy, participant reached protocol-defined stopping criteria or trial closed/terminated. All the above are at the discretion of CI/PI.

In addition participants must be  $\geq 70\%$  to  $\leq 100\%$  compliant on taking trial medication between each on-treatment visits. Participants who fall outside this range should be re-educated on treatment compliance. In assessing compliance, it should be noted that participants may discontinue their use of trial drug due to an exacerbation. See section 10.5.3 for further information concerning participants' withdrawal due to exacerbation.

Specific withdrawal criteria relating to biochemistry, ECG abnormalities and exacerbation of COPD are listed below. Participants who are withdrawn from the trial will be replaced at the discretion of the CI/PI.

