### 10.5.2 ECG

Participant that meets the criteria below will be withdrawn from the trial. The QT correction formula used to determine discontinuation should be the same one used throughout the trial.

For participants with underlying bundle branch block, follow the criteria listed below:

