### **11.13 Treatment of IMP Overdose**

Any signs or symptoms of overdose will be treated symptomatically. No specific antidote is known and the investigator will use clinical judgment. Participants that have taken an overdose of IMP will be withdrawn from the trial.

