## **13 Assessment of Safety**

### **13.1 Safety Reporting Definitions**

The investigator or trial staff are responsible for detecting, documenting and reporting events that meet the definition of an AE or SAE.

AEs will be recorded from the start of IMP dosing V3 (Day1), V4, V5, V6, V7 (Days 14/28/56/84 (All  $\pm$  96h)), V8 (Days 105-111), V9 (Days 109-112) and until the follow-up V10 (Days 120-126).

SAEs will be collected over the same time period as stated above for AEs. However, any SAEs assessed as related to trial participation (e.g. trial treatment, protocol-mandated procedures, invasive tests, or change in existing therapy) or related to a GSK product will be recorded from the time a participant consents to participate in the trial up to and including any follow-up visit. All SAEs will be recorded and reported to sponsor/CI and GSK within 24 hours of awareness, as indicated in TPM.

Investigators are not obligated to actively seek AEs or SAEs in former trial participants. However, if the investigator learns of any SAE, including a death, at any time after a participant has been discharged from the trial, and he/she considers the event reasonably related to the IMP or trial participation, the investigator would promptly notify sponsor/CI and GSK.

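### QTc, overdose and SUSAR stops are written as leaving the trial, and V10 has no workable timing for a participant stopped before the second scan (minor, cheap to mend)

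*Protocol*

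**What the plan says.** Three safety stops are worded as exit from the trial:

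- QTc, section 10.5.2: "Participant that meets the criteria below will be withdrawn from the trial". The note under Table 1 likewise speaks of discontinuing the subject from the trial.
- Overdose, section 11.13: "Participants that have taken an overdose of IMP will be withdrawn from the trial".
- SUSAR, synopsis: "Participants will be withdrawn from the trial if they experience a SUSAR". Section 10.5 lists SUSAR among possible withdrawal reasons, all at CI/PI discretion: "Primary reasons for withdrawal may include: SUSAR, adverse event, withdrawal of consent, lost to follow-up".

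Two other kinds of stop are handled differently. For liver chemistry, section 10.5.1 stops IMP, and section 14 has the participant leave the trial only when safety follow-up is finished. For COPD exacerbation, section 10.5.3 has a withdrawn participant followed until the exacerbation resolves.

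Section 13.1 records AEs and SAEs from first dose to V10, and adds: "Investigators are not obligated to actively seek AEs or SAEs in former trial participants".

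Section 12.1.6 fixes V10 at Days 120-126 and describes it by reference to imaging: "Participants will return to the unit within approximately 1-2 weeks after the last scan". Its content is a physical examination with BP and heart rate, bloods, urine, biomarkers, and AE and concomitant medication checks.

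**The concern.** Safety is a secondary endpoint, and the Safety Population in section 16.2 is everyone dosed. The participants who say most about tolerability are those who had to stop. Under the stated exit rule, someone stopped for QTc, overdose or a SUSAR leaves the trial at once, and from then on events need not be actively looked for. The one scheduled safety visit after treatment is timed from a scan that such a person may never have.

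The event that triggers the stop is recorded. What may go unrecorded is a later or separate event and, outside the SUSAR reporting duties, the resolution of the triggering one. The protocol already contains a better sequence for liver events, so the issue is uneven wording within one document.

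**Working it through.** **Inputs.** V2 scan Days -14 to -1; V8 scan Days 105-111; V9 Days 109-112; V10 Days 120-126 (sections 12.1.3 to 12.1.6, Table 7). Maximum treatment 112 days (11.4.2). Terminal half-life about 10 h (11.2.3). Scheduled ECGs at V1, V3 (before dosing) and V9 only (12.1, Table 7).

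**Step 1: the plan's own V10 timing, for completers.**
- Scan plus 7 to 14 days: 105 + 7 = 112 to 105 + 14 = 119 for the earliest scan; 111 + 7 = 118 to 111 + 14 = 125 for the latest.
- Days 120-126 measured from the scan: 120 - 111 = 9 to 126 - 105 = 21 days. The two descriptions of V10 do not fully agree (a Day 105 scan gives Days 112-119, before the window opens), but completers are still seen.
- Measured from V9: 120 - 112 = 8 to 126 - 109 = 17 days. For completers this is a sensible interval.

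**Step 2: the same timing for someone stopped before V8.**
- Scan anchor: the only scan is V2, so V10 would fall between -14 + 7 = Day -7 and -1 + 14 = Day 13 (Day 14 if there is no Day 0). That is before dosing or within about the first two weeks of it, and unrelated to the stop.
- Calendar anchor: for a stop on Day 28, 120 - 28 = 92 to 126 - 28 = 98 days later; for Day 84, 120 - 84 = 36 to 126 - 84 = 42 days later.
- Neither anchor gives a visit soon after the last dose. No early-termination visit is defined in the visible text, and nothing there sends a withdrawn participant to V10.

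**Step 3: the exit rules side by side.**

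| Stop | What ends first | Follow-up stated |
|---|---|---|
| Liver (10.5.1, 14) | IMP | Yes, before trial withdrawal |
| Exacerbation (10.5.3) | Participation | Yes, to resolution |
| SUSAR (synopsis, 13.5) | Participation | Information to be sought; no visit |
| Overdose (11.13) | Participation | Symptomatic treatment; no visit |
| QTc (10.5.2) | Participation | None stated |

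Section 14 places trial withdrawal after safety follow-up. The protocol therefore treats withdrawal as the point where follow-up ends, unless it says otherwise, as 10.5.3 does.

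**Step 4: how far QTc is affected.** The only scheduled ECG after dosing starts is at V9. A QTc stop found there falls 8-17 days before V10, so the timing works. A QTc stop before V8 can arise only from an unscheduled ECG.

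**Step 5: what a visit would show.** At 7 to 14 days after the last dose, 7 x 24 / 10 = 16.8 to 14 x 24 / 10 = 33.6 half-lives have passed. The visit documents recovery and later events, not drug exposure.

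**The case against.** The strongest reply is that the protocol never equates a withdrawn participant with a former one. Section 13.1 speaks of former participants in connection with discharge from the trial, records AEs up to V10 without exempting anyone withdrawn, and nowhere forbids attending V10. Section 10.5.3 shows that a withdrawn participant can still be followed. The section 6 flow chart and the Trial Procedures Manual, to which detail is deferred, are not available here. This stands in part: the text is silent on V10 after withdrawal, and it cannot be said that no follow-up rule exists anywhere. But section 14's order of events supports reading trial withdrawal as the end of follow-up, and the V10 timing in 12.1.6 is stated and does not fit an early stopper.

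The second reply is that much is covered already, and this largely stands. SUSAR follow-up information must be sought or provided (13.5.2, 13.5.3.2), signs and sequelae of a suspected overdose are reportable AEs (13.1.1), extra laboratory tests are allowed at the discretion of the PI or medical monitor (12.2), and late related SAEs are reported if the investigator learns of them (13.1). None of these is a scheduled visit, but together they confine the gap mainly to later or other events.

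A reader might also infer that every SAE or AE stop is a trial exit. The documents do not say so. The synopsis leaves SAE withdrawal to PI/CI discretion ("participants will be withdrawn if they experience a SAE, which would affect their ability to participate in the trial"), and 10.5 does the same for adverse events.

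**Conclusion.** The point holds as a minor, cheap improvement. For QTc, overdose and SUSAR stops before V8, the visible text ends participation without first requiring safety follow-up, and V10 is anchored to events that do not fit these participants. The practical gap is mainly later or other events after a SUSAR, an overdose or a QTc stop from an unscheduled ECG. Completers and the PET analysis are not affected.

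Three stronger readings are not supported. The intervals of 36 days or more between an early stop and V10 do not measure harm: they apply only if the person does attend in the calendar window, in which case they are observed for longer after the last dose than a completer. The protocol gives no rate for these stops, so no count of affected participants can be derived. The absence of an ECG at V10 is not in itself a defect: V10 falls many half-lives after dosing, and 10.5.2 already requires repeat ECGs before a QTc withdrawal.

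The conclusion assumes that withdrawal from the trial makes someone a former participant under 13.1, and that the flow chart and Trial Procedures Manual contain no contrary rule.

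**What to change.** In 10.5.2, 11.13 and the synopsis, replace withdrawal from the trial with: *IMP permanently stopped; withdrawn from the trial after safety follow-up*. This is the order already used in section 14.

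In 12.1.6, hold the existing V10 assessments about 1-2 weeks after the last dose for every dosed participant who has not withdrawn consent, keeping Days 120-126 for completers. Taking 8-14 days as an example, a stop on Day 28 gives a visit on Days 28 + 8 = 36 to 28 + 14 = 42; a stop on Day 84 gives Days 92-98; a last dose on Day 112 gives Days 120-126, as now.

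A repeat ECG at that visit after a QTc stop is optional. No extra imaging is needed. The cost is amendment wording and one already-specified visit for the few who stop early, some of whom may decline to attend.

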## **12.2 Clinical laboratory assessments**

Blood samples for clinical chemistry (including liver function tests [ALT, AST, bilirubin and creatine Phosphokinase]), hematology and urine samples will be collected multiple times throughout the trial. Participants are required to fast overnight prior to these blood collections since measurement of glucose and cholesterol fractionation must occur in a fasted state. In addition to the below-mentioned haematology, clinical chemistry and urinalysis labs, additional lab studies may be performed as deemed necessary by the PI or medical monitor for the purpose of clinical evaluation or safety monitoring.

### **Haematology**

Haemoglobin, Hematocrit, Platelets, Total White Blood cells (WBC), Neutrophils, Lymphocytes, Monocytes, Eosinophils, Basophils, and Fibrinogen.

#### Clinical Chemistry

Sodium, Potassium, Glucose, Creatinine, Bilirubin (total; direct and indirect will be reported if total is > 2ULN), Alanine transaminase (ALT),  $\gamma$ -glutamyl transferase (Gamma GT), Alkaline Phosphatase, urea uric acid, HbA1C and hsCRP.

#### Lipid Profile

Triglycerides, Cholesterol, High Density lipoprotein (HDL) and Low Density lipoprotein (LDL) will also be measured on V3 and V9.

#### Urinalysis

Approximately, 10-20ml mid-stream urine will be collected into a sterile container and will be screened by dipstick for: Protein, Ketones, Glucose, RBC, WBC.

Serum storage for up to 5 years for further analysis or trial close, whichever is sooner.

### 12.3 Pregnancy

The investigator will attempt to collect pregnancy information on any female partner of a male trial participant who becomes pregnant while participating in this trial. The investigator will record pregnancy information on the appropriate form and submit it to the sponsor and GSK of learning of the partner's pregnancy. The partner will also be followed to determine the outcome of the pregnancy. Information on the status of the mother and child will be forwarded to the sponsor and GSK. Generally, follow-up will be no longer than 6 to 8 weeks following the estimated delivery date. Any premature termination of the pregnancy will be reported.

#### 12.4.2 MRI

All MRI scans will be conducted by experienced radiographers and radiologists in the nominated scanning sites. Where possible, the same machine will be used for both MRIs on a particular participant (although the machine used may differ between participants at different scanning sites).

Contraindications to MRIs will be determined at the time of participant screening according to local clinical guidelines. Baseline MRI scanning will be performed in eligible participants between the index FDG-PET/CT scan and first drug dosing. Follow-up scans will be undertaken within a week of the final PET/CT scan at 16 weeks. Scanning duration is estimated to be no longer than 90 minutes per participant.

Participants unwilling or unsuitable for the MRI may still take part in the main study.

Detailed information on the MRI scan is provided in the TPM.

### 12.5 Non Imaging End Points

#### 12.5.1 Flow mediated dilatation

Endothelial function will be assessed in the brachial artery of the non-dominant arm using the technique of flow mediated dilatation. Vessel diameter will be measured, using high-resolution vascular ultrasound with a 5-20MHz linear-array transducer, continuously for 1 minute at baseline, and for a further 5 minutes following release of a cuff inflated to 200mmHg, placed distal to the ultrasound probe. After return to baseline, vessel diameter will be measured continuously for 5 minutes following administration of 25µg of sublingual glyceryl trinitrate (GTN). FMD is defined as the maximum percentage increase in vessel diameter during reactive hyperemia; GTN-mediated dilatation is defined as the maximum percentage increase in vessel diameter after sublingual GTN. This is a standard technique.

Additional details on the procedure are provided in the TPM.

### **12.5.2 Muscle Assessments**

Inspiratory muscle strength will be measured as maximal SNIP. The largest of a minimum 5 efforts will be recorded.

### **12.5.3 Arterial haemodynamics**

Blood pressure will be measured in the dominant arm using a validated oscillometric technique (BHS validation) following 5 minutes of seated rest. Measurements will be made in triplicate and the average of the last 2 will be used for analysis. Additional readings will be made if there is an error or an erroneous reading. Heart rate will also be recorded. Following this, a high-fidelity micro manometer will be used to obtain accurate readings of the peripheral radial pressure waveforms for arterial haemodynamics in the seated position by flattening, but not occluding, the radial artery of the dominant arm using gentle pressure. Data will be collected to produce a central pressure waveform. Augmentation represents the difference between the second and first systolic peaks of the central pressure waveform. AIx is defined as the augmentation expressed as a percentage of the overall pulse pressure. Heart rate will also be reported, MAP and central pressure.

Following 15 minutes supine rest BP will be recorded as detailed above. Aortic Pulse wave velocity (PWV) will then be determined between the carotid and femoral arteries using a non-invasive pressure sensor and ECG gating, and reported together with heart rate and calculated MAP. Additional readings will be made if there is an error or erroneous reading.

More detailed information on how to perform this procedure is listed in the TPM.

### **12.6 Six minute walk test**

A 6 minute walk test will be conducted in all participants to assess exercise tolerance, according to ATS guidelines. This is a simple, self-paced exercise test, where participants are asked to walk at their own pace for 6 minutes, including breaks if necessary. The distance covered on a flat, hard surface (ie. walking track) with minimal blind turns or obstacles will be recorded as the 6 minute walking distance.

### **12.7 Blood Sampling**

Blood samples will be collected on all visits. Blood samples will be collected pre-dose, following an overnight fast.

Blood samples will be collected to analyze established inflammatory biomarkers, at the cellular (total blood leukocytes, blood neutrophils) and protein level (e.g. hsCRP, plasma fibrinogen) but not limited to these.

After completion of the clinical trial, investigations may be performed on samples collected during the course of the trial to detect factors or profiles that correlate with other measures of response to treatment with Losmapimod. The resultant data may also be of application for medically related conditions.

- Performance of these investigations may be conditional on the results of the clinical trial principally, but not exclusively, on the primary measures of the clinical trial outcome and samples may be selected for analysis on the basis of the trial outcome.

Comparative examination of pre-dosing profiles of participants may uncover known or novel candidate biomarkers/profiles which could be used to predict response to treatment

with Losmapimod or provide new insights into medically related conditions. Comparative examination of post-dosing profiles in conjunction with pre-dosing profiles may yield known and novel candidate biomarkers/profiles and new insights which relate to the action of Losmapimod.

All other samples will be retained for a maximum of 5 years after the last participant completes the trial.

Please refer to the TPM for sample processing information.

## **12.8 Trial restrictions**

### **12.8.1 Meal and Dietary Restrictions**

Participants will be asked to abstain from ingestion of alcohol and caffeine 12 hours prior to the first dose of trial medication and until collection of the final blood sample at each individual trial visit. Participants will be required to fast overnight prior to each clinical chemistry and haematology blood sample collection. Participants undergoing FDG-PET/CT and  $\pm$  MRI scanning will be required to fast for 6 hours prior to scanning. Previous studies have not identified a major effect of food in the systemic exposure of Losmapimod; therefore, there are no food restrictions other than the ones indicated above.

### **12.8.2 Other Restrictions**

Participants should abstain from strenuous physical activity for 72 hours prior to each blood collection for clinical laboratory tests. Participants who are smokers will be unable to smoke for the duration of each trial visit. Participants will be required to fast for 6 hours before scanning and restrict exercise for 24 hours before FDG-PET/CT and  $\pm$  MRI scanning.

